## Abstract

Fibromyalgia is a complex chronic disorder involving persistent widespread pain accompanied by functional limitations, cognitive impairments, and alterations in neural processing. Previous research indicates that exercise-based interventions can play a key role in alleviating symptom burden and enhancing physical performance; however, there is limited evidence regarding their impact on neurophysiological mechanisms. Creative dance, in combination with strength training, may stimulate both motor and cognitive systems, promoting brain plasticity and functional improvements. This study will analyze the effects of a six-week strength and creative dance program on physical fitness under single- and dual-task conditions in women with fibromyalgia and will explore the associated changes in brain electrical activity and autonomic modulation. Methods: This randomized controlled trial will be divided into an exercise group (*n* = 22) and a control group (*n* = 22). The 6-week supervised intervention consists of two 60-min sessions per week, combining strength exercises and creative dance. Primary outcomes include physical fitness tests (strength, mobility, balance, and agility gait test in single-task and dual-task), fibromyalgia symptoms, and quality of life. Secondary outcomes include changes in electroencephalography, heart rate variability, physical activity level, and fear of falling. Statistical analyses will compare within- and between-group differences using non-parametric tests and effect sizes. It is hypothesized that the intervention will improve physical fitness and dual-task performance, alongside increases in brain activity power. This study may provide insights into the neurophysiological mechanisms underlying the benefits of exercise benefits in fibromyalgia.

## 1. Introduction

Fibromyalgia (FM) is a long-term rheumatic condition of unclear etiology that predominantly affects women. It is characterized by widespread musculoskeletal pain as well as reduced physical capacity, balance impairments, fatigue, depression, anxiety, and sleep disturbances [1]. Individuals with FM who present a high risk or fear of falling [2] tend to reduce their motor activities, generating a cycle of physical deterioration, decreased quality of life, loss of autonomy, and a greater degree of disability [3].

Physical exercise has been shown to reduce pain [4], symptom severity, and fatigue [5] as well as to improve quality of life, physical fitness, sleep [5], and psychological well-being [5]. Multicomponent programs that combine aerobic and strength exercises are particularly effective for decreasing pain and enhancing both physical and mental health. Other modalities, such as whole-body vibration [6], aquatic exercise [7] or virtual reality-based interventions, have also demonstrated benefits in functional capacity, along with a reduction in both the risk and fear of falling.

Among the most recent interventions, dance-based therapies have emerged as a promising alternative capable of improving pain, quality of life, depressive symptoms, and the overall impact of the disease [8]. Two main approaches can be distinguished: (a) repetitive dance, focused on performing structured movement sequences such as aerobic dance or Zumba, and (b) creative or improvised dance, based on the free expression of bodily movement, as in biodance, aquatic dance, or dance movement therapy. Both types of dance have been shown to improve overall physical condition and reduce pain [9] as well as mitigate the impact of disease and contribute to improvements in health-related quality of life, although some studies suggest that creative dance may be more effective [8]. From a physical perspective, dance promotes balance, coordination, strength, flexibility, aerobic capacity, and proprioception [10]. At the cognitive level, it enhances attention, memory, and decision making [10], while in the psychosocial domain, it fosters motivation, emotional expression, and social interaction [11]. Altogether, dance constitutes a comprehensive intervention that simultaneously stimulates the motor, sensory, and cognitive systems, producing positive effects on mood, daily functioning, and social life. Therefore, dance supports brain plasticity [12] and contributes to overall improvements in function and quality of life in individuals with FM.

Studies in older adults indicate that dance-based interventions are associated with structural and functional brain changes in regions involved in executive function, attention, and cognitive control as well as with increased levels of brain-derived neurotrophic factor, supporting their role in neuroplasticity [10]. In individuals with fibromyalgia, exercise-based interventions have been shown to modulate brain electrical activity, including changes in beta band [13], which may contribute to improvements in cognitive performance and the normalization of altered neural oscillations associated with pain [14] and cognitive dysfunction [15].

Beyond static neurophysiological measures, the integration of perception and action represents a relevant framework for understanding exercise-related adaptations in real-life contexts. Dual-task paradigms, which reflect everyday functional demands, may be particularly sensitive to changes induced by dance-based interventions. The theoretical interpretation of these mechanisms, including their relation to stimulus–response integration models such as the Binding and Retrieval in Action Control (BRAC) framework, is further addressed in the expected mechanisms section.

Previous research supports the feasibility and effectiveness of relatively short-duration (six weeks) exercise interventions in FM. In this regard, Casanova-Rodríguez et al. [16] reported that statistically significant differences can be observed in aerobic exercise programs lasting from three to twenty-four weeks, and this duration range has also been applied in strength training interventions [17]. Taken together, these findings suggest that a six-week intervention period is enough to produce clinically meaningful changes and is supported by evidence in the FM literature.

However, despite growing evidence supporting the benefits of creative dance-based and multicomponent exercise interventions in fibromyalgia, no previous studies have simultaneously examined their effects on physical performance under single- and dual-task conditions together with resting-state EEG markers of neuroplasticity, particularly alpha and theta activity. Overall, these findings support the use of a multidimensional intervention combining strength training and creative dance to target both physical and cognitive impairments in individuals with FM, forming the basis for the purposes of the present study.

Objectives:(a)To analyze the effects of a 6-week physical exercise training program based on creative dance combined with strength training on physical fitness (strength, mobility, balance, functional capacity, and gait agility) under both single- and dual-task conditions in individuals with FM;(b)To investigate exercise-related changes in resting-state brain electrical activity and HRV as a secondary outcome, with a primary focus on beta power, in order to explore potential neurophysiological mechanisms underlying functional improvements.

Hypotheses:
**H1.** Six weeks of strength training and creative dance are expected to significantly improve physical fitness (strength, mobility, balance, functional capacity, and gait agility) in individuals with FM, under both single- and dual-task conditions, compared with their baseline status and a control group.**H2.** It is hypothesized, for exploratory purposes, that the physical exercise intervention will be associated with specific changes in resting-state brain electrical activity, characterized primarily by increased beta power, that could be related to increased cerebral blood flow [13]. Also, the autonomic modulation would be enhanced [18].

## 2. Materials and Methods

### 2.1. Study Design

This study will be a randomized controlled trial with a parallel group design (pretest–post-test control group design) [19]. Participants will be recruited from FM associations in the region of Extremadura (Cáceres, Almendralejo, Hervás and Olivenza) in Spain. Each FM association will be randomly assigned to either the intervention group, which will participate in a structured physical activity program or to the control group. To ensure methodological rigor and high-quality reporting consistency with clinical trial standards, the study will follow the SPIRIT 2013 Statement guidelines and will apply the TESTEX 2015 scale, a tool specifically developed to evaluate the quality and reporting standards of exercise training studies [20].

### 2.2. Participants

#### 2.2.1. Eligibility Criteria

To be eligible for participation, individuals must meet the following inclusion criteria: (a) women with a clinical diagnosis of FM provided by a rheumatologist according to the American College of Rheumatology criteria [21]; (b) ability to ambulate independently without assistance; (c) be able to communicate with the research staff; and (d) have read, understood, and signed the informed consent form. The exclusion criteria will be (a) the presence of psychiatric or neurological conditions; (b) current or past substance abuse or dependence; (c) contraindication for physical exertion; (d) severe fractures or musculoskeletal injuries within the previous six months; (e) being pregnant; (f) active or ongoing ear diseases or infections that may affect balance; and (g) any other condition that could impair balance.

#### 2.2.2. Recruitment

The sample size will be calculated based on one of the study’s primary outcomes, i.e., the impact of FM. Data from a previous study [22] that will be used as a reference evaluated the effects of a creative dance intervention on this outcome. In that study, the impact of FM was reduced by 1.16 points compared with the control group after six weeks of intervention.

According to the results obtained in the G*Power statistical power analysis software version 3.1.9.7 (Heinrich Heine University Düsseldorf, Düsseldorf, Germany), assuming an effect size of f(V) = 0.98, a power of 85%, and a significance level of 0.05, a sample size of 22 people per intervention group is estimated. However, considering an anticipated dropout rate of 10%, a total of 44 participants (22 per group) will be needed to observe a significant effect.

Therefore, the participants recruitment will take place between January and March 2026. Both groups will consist of women with FM (exercise group: *n* = 22; and control group: *n* = 22) recruited from different FM associations in the region of Extremadura.

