### 2.12. Outcome

#### 2.12.1. Primary Outcomes Measures (Confirmatory Analyses)

(A)Questionnaires

Impact of the Disease

The FM Impact Questionnaire Revised (FIQR) [28] is a self-administered instrument composed of 21 items. Each item is rated on a 0–10 scale, with higher scores indicating greater disease impact. The questionnaire is structured into three domains: (a) function, (b) overall impact, and (c) symptoms. The total score, obtained by summing the three domains, ranges from 0 to 100, with higher values reflecting a greater overall impact of FM. In this study, the validated Spanish version of the FIQR [29] will be applied.

Health-Related Quality of Life

The EuroQol-5 dimensions 5 levels (EQ-5D-5L) measures health-related quality of life across five domains (mobility, self-care, usual activities, pain/discomfort, and anxiety/depression), each with five response levels. It also includes a visual analog scale ranging from 0 (worst health) to 100 (best health). The instrument has been validated in Spanish populations [30].

(B)Physical Fitness

Handgrip Strength

The Handgrip Strength (HGS) test will be used to assess maximal isometric hand strength. Participants will stand upright with their elbow extended at hip height and exert maximal force on a hand-held dynamometer (Takei TKK 5401, Takei Scientific Instruments Co., Ltd., Tokyo, Japan) featuring analog grip and adjustable handle to accommodate various hand sizes. Two repetitions will be performed for each hand, with a one-min rest interval between attempts. The highest value from each hand will be used for analysis [31].

Timed Up and Go

The Timed Up and Go (TUG) test is a dynamic test of mobility and balance in which participants rise from a chair without using their hands, walk 3 m as quickly as possible without running, turn around a cone, return to the chair, and sit down [32]. Performance is measured as the time taken to complete the task with ChronoJump software (version 2.2.0 Barcelona, Spain) and Chronopic hardware (DIN A-4, 210 × 297 mm), which will be placed on the backrest of the chair; one practice trial will be allowed for familiarization, after which the test will begin with the command “Ready, go”.

Short Physical Performance Battery

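### The sample-size statement contradicts itself: 22 per group both before and after 10% dropout, an effect size f(V) = 0.98 that does not give 44, and no shown step from 1.16 points to 0.98

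*Protocol article*

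**What the plan says.** Section 2.2.2 (Recruitment) is the only place where the protocol article justifies the number of participants. The basis is a single outcome: "The sample size will be calculated based on one of the study’s primary outcomes, i.e., the impact of FM". The reference is an earlier creative dance study in which "the impact of FM was reduced by 1.16 points compared with the control group after six weeks of intervention". The article names no instrument, score range or SD for that study.

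The G*Power inputs are then given as "assuming an effect size of f(V) = 0.98", with "a power of 85%, and a significance level of 0.05". The test family, the specific test and whether it is one- or two-sided are not stated. The reported result is 22 per group. The next sentence brings in the dropout allowance: "considering an anticipated dropout rate of 10%, a total of 44 participants (22 per group) will be needed to observe a significant effect".

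Section 2.12.1 says how this trial measures disease impact, namely by the FIQR: "The total score, obtained by summing the three domains, ranges from 0 to 100". Section 4.3 (Limitations) then describes the trial as adequately powered for its primary outcomes.

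**The concern.** Three steps in one short calculation do not fit together.

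- **Dropout.** An allowance for 10% loss should separate the number analysed from the number recruited. Here both are 22 per group, so either no allowance was added or the figure before it is misprinted.
- **Effect-size metric.** f(V) is on the scale of Cohen's f. For two equal groups f is half of d, so f(V) = 0.98 is a difference of nearly two SDs. That would need far fewer than 44 people.
- **Source of the effect.** A raw difference of 1.16 points is followed by a standardised effect of 0.98 with no SD between them, and the trial's own outcome runs from 0 to 100.

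This is the trial's only power statement, and the claim in section 4.3 depends on it. As printed, a reader cannot tell whether the planned effect is d = 0.98 or d = 1.96, whether 20 or 22 per group must be evaluable, or what FIQR difference the trial was designed to detect.

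**Working it through.** **Inputs from section 2.2.2:** effect size 0.98 labelled f(V); power 85%; alpha 0.05 (two-sided assumed, as the article does not say); 22 per group; dropout 10%; reference difference 1.16 points. **From section 2.12.1:** FIQR range 0 to 100. All power figures below ignore clustering by association.

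**1. The plan's figure, with the effect size as labelled.** With two groups and two time points, the multivariate group-by-time test is an F-test with 1 and N − 2 degrees of freedom. Its non-centrality is λ = f² × N, and f² = 0.98² = 0.9604.

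| Total N | λ | Power |
|---|---|---|
| 10 | 9.6 | 77.5% |
| 12 | 11.5 | 86.3% |
| 44 | 42.3 | above 99.9% |

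With the alternative convention λ = f² × (N − 2), N = 14 gives λ = 0.9604 × 12 = 11.5 and power 87.6%. The stated inputs therefore lead to 12 to 14 people in total. Working backwards, 85% power at N = 44 corresponds to f = 0.46, that is d = 0.92.

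**2. The plan's figure, with 0.98 read as Cohen's d.** Two-sample t-test, two-sided, 2n − 2 degrees of freedom, non-centrality d × √(n/2).

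| n per group | Power |
|---|---|
| 19 | 83.6% |
| 20 | 85.5% |
| 22 | 88.8% |

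The evaluable need is 20 per group. A Mann–Whitney test needs 21 per group (relative efficiency 0.955) or 23 (relative efficiency 0.864). A one-sided t-test needs 16. So d = 0.98 gives numbers near 22, while f(V) = 0.98 does not.

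**3. The dropout step.**
- If 22 per group must be evaluable: 22 / 0.9 = 24.4, so 25 per group, 50 in total.
- If 22 per group are recruited: 22 × 0.9 = 19.8, about 20 per group evaluable.
- If 20 per group must be evaluable: 20 / 0.9 = 22.2, so 23 per group by division. The figure 22 comes only from 20 × 1.1, and it leaves 19.8.

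None of these has 22 on both sides of the allowance.

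**4. From 1.16 points to 0.98.** The SD that links them is difference / d.
- 0.98 as d: 1.16 / 0.98 = 1.18 points.
- 0.98 as f, so d = 2 × 0.98 = 1.96: 1.16 / 1.96 = 0.59 points.

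On a 0 to 100 total, an SD of 1.18 is about 1% of the range.

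**The case against.** The strongest defence is that the final number may be right. If 0.98 is Cohen's d with the wrong label, a two-sided t-test needs 20 per group, and 20 × 1.1 = 22 gives the 44 stated. The errors would then be one label and one figure, 20 misprinted as 22. If 0.98 really is f(V), 44 is far more than needed. This stands: neither reading of 0.98 shows a material shortfall before clustering. It does not rescue the paragraph, because recovering 44 means changing two printed items. Nor can the reader choose the repair. A rank test at d = 0.98 needs 21 to 23, which would make 22 an evaluable number with no allowance added.

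One f(V) calculation does produce the number 22: a global MANOVA with five responses. That is 22 in total, not per group, and the section sizes the trial on one outcome.

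On the 1.16 points, a reader might infer that this difference is impossible on the trial's scale, or might divide it by a typical SD for a 0 to 100 score and conclude that the trial has almost no power. The documents support neither. They give no instrument, range or SD for the reference study, and the 0 to 100 range describes only this trial's FIQR. If the reference score used a shorter scale, an SD near 1.2 could be ordinary, and a standardised effect can be carried from one scale to another. What stands is narrower: the step is not shown, and it is implausible if the points are FIQR points.

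It can also be said that a journal article may leave the SD and target difference to the full protocol. As an omission alone that would be fair. Here the article prints a raw difference and a standardised effect that do not fit each other on the outcome it names.

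**Conclusion.** The sample-size statement is wrong as written, in two respects that need no outside information. It gives 22 per group both before and after a 10% allowance, where 22 evaluable would mean 25 recruited and 22 recruited means about 20 evaluable. And f(V) = 0.98 leads to 12 to 14 people in total rather than 44, at which power would exceed 99.9%. Cohen's d = 0.98 gives a figure near the stated one (20 per group, 85.5%), so mislabelling is the likely explanation, but only the sponsor can confirm it.

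The third element is weaker. The link from 1.16 points to 0.98 is undocumented, and on the 0 to 100 FIQR it would need an SD of about 1.2 points (0.6 if 0.98 is f). The reference score was therefore probably on another scale, though the documents do not prove this.

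It does not follow that the trial is too small on these inputs. With 44 recruited and 10% lost, about 20 per group remain, and power is about 85% if d = 0.98. These figures assume a two-sided test at 0.05 and equal groups. They leave out clustering by association, which is a separate matter.

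**What to change.** The sponsor should go back to the saved G*Power run and rewrite section 2.2.2 from it. The metric should not be back-fitted to reach 44. The paragraph should state:

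- the effect-size metric actually entered, the test family and test, and whether it was one- or two-sided;
- the evaluable number per group that the run returned;
- the recruited number per group after 10% dropout, as a separate figure, with the inflation rule used;
- the scale and SD behind the 1.16 points, and how they lead to the effect size.

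If the planned 44 is kept, say that about 20 per group are expected to be evaluable and give the power at that number: about 85% if d = 0.98, before any clustering penalty. The statement on adequate power in section 4.3 should then refer to that figure.

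The cost is checking one software run and rewording one paragraph. No added patients are required.

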### 2.3. Randomization of Assessments

The assessments will follow a fixed sequence with alternating tests of the upper and lower limbs, thereby ensuring adequate rest periods to prevent cumulative fatigue and optimizing the overall time required for the evaluations. To reduce familiarization and learning effects, the sequence of specific conditions will be randomized. Randomization will apply to both the physical test conditions and the arithmetic cognitive task.

The physical tasks that each participant will complete at baseline (pre) and post-intervention will be scheduled across two assessment days:Day 1: Cognitive task (arithmetic-based counting test), handgrip strength, timed up and go test (TUG), arm curl test (ACT), and 30 s chair stand test (CST). Randomization: The random allocation sequence will be generated by an independent researcher using a computer-based random number generator (Random Number Generator tool; Google, LLC., Mountain View, CA, USA) and implemented via a password-protected Excel file. Simple randomization (0/1) will be used for Day 1 tasks. Personnel responsible for enrolling participants and conducting assessments will remain blinded to the random allocation sequence. Two aspects will be randomized for each participant: (1) whether the arithmetic subtraction task is performed at the beginning (coded as 1) or at the end (coded as 0) of the physical test sequence and (2) whether the motor task is performed as a single-task condition (coded as 0) or as a dual-task combined with the cognitive subtraction task (coded as 1). The handgrip test will be performed without dual-task condition due to its temporal execution characteristics;Day 2: Baseline resting Electroencephalography (EEG) and Heart Rate Variability (HRV), EEG and HRV combined with the Stimulus–Response (S-R) paradigm protocol, Short Physical Performance Battery (SPPB), and Agility Challenge for the Elderly (ACE). Randomization: Only the spatial orientation component of the ACE test will be randomized according to the recommendations of Lichtenstein et al. [23]. The random allocation sequence for this task will also be generated by the independent researcher, recorded in the same password-protected Excel file, and accessed by the researcher immediately prior to testing to ensure allocation concealment

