### 2.7. Procedures

Figure 1 illustrates the study timeline and the sequence of the interventions. Initially, anthropometric measurements will be obtained to calculate participants’ body mass index (BMI). Subsequently, participants will provide sociodemographic information and will complete the following questionnaires: the International Physical Activity Questionnaire (IPAQ); the FM Impact Questionnaire-Revised (FIQ-R); the Falls of Efficacy Scale International (FES-I); the EuroQol 5 dimensions-5 levels (EQ-5D-5L); and the EQ-Health and Wellbeing (EQ-HWB and EQ-HWB-9).

Pre-intervention and post-intervention assessments: On the first day, after completing the questionnaires, participants will undergo a cognitive assessment using the Montreal Cognitive Assessment (MoCA). This will be followed by the physical (strength and mobility test) and cognitive task, which will be administered under both single-task and dual-task conditions. On the second day, the following assessments will be conducted: (1) a 5-min baseline resting EEG, (2) Stimulus–Response (S-R) paradigm, and (3) physical performance tasks, including balance and agility gait tests.

All physical performance and outcome assessments will be conducted by evaluators blinded to participants’ group allocation, as described in Section 2.4.

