### 2.13. Data Analysis

The collected outcomes will be compiled in an anonymized database for statistical processing. Both descriptive statistics and inferential analyses will be conducted. Data analysis will be performed using the Statistical Package for the Social Sciences software (SPSS, version 25.0; IBM Corp., Armonk, NY, USA). The Shapiro–Wilk and Kolmogorov–Smirnov test will be used to assess the normality of all variables.

Furthermore, to explore the effect of physical exercise intervention, physical performance tests will be analyzed under both single task and dual-task conditions. Dual-task cost will be calculated to quantify the impact of performing a cognitive task on physical performance. Given the cluster-randomized design, changes over time and between-group differences were analyzed using linear mixed-effects models, accounting for the hierarchical structure of the data, with participants nested within fibromyalgia associations. Group (intervention vs. control), time, and their interaction (group × time) were included as fixed effects. Random intercepts were specified for associations and for participants, and random slopes were included when appropriate, assuming an unstructured covariance matrix. The normality of model residuals was visually assessed for all variables.

To quantify the degree of clustering, the intra-cluster correlation coefficient (ICC) will estimate from the variance components of the mixed-effects models, calculated as the ratio of between-association variance to total variance (between-association plus residual variance). This parameter will be used to evaluate the magnitude of within-association dependence and to confirm the appropriateness of the cluster-adjusted analytical approach.

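### The Day 1 code in Section 2.3 assigns a task condition where the rest of the protocol needs an order of conditions

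*Protocol article*

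**What the plan says.** Section 2.3 gives the purpose of the Day 1 randomisation: "To reduce familiarization and learning effects, the sequence of specific conditions will be randomized". It gives the method as "Simple randomization (0/1) will be used for Day 1 tasks", and the unit as "Two aspects will be randomized for each participant".

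The two coded items are then defined:
- Item (1) is a position: the subtraction task comes before (1) or after (0) the physical tests.
- Item (2) is "whether the motor task is performed as a single-task condition (coded as 0) or as a dual-task combined with the cognitive subtraction task (coded as"; the quote stops just before the dual-task code, which is 1. Handgrip is exempt.

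Three other places bear on item (2):
- Section 2.7 describes the Day 1 physical and cognitive tasks as ones "which will be administered under both single-task and dual-task conditions".
- Section 2.12.1 lists the dual-task condition among the primary outcomes and applies it to three tests: TUG, ACT and CST.
- Section 2.13 analyses the physical tests under both conditions and adds: "Dual-task cost will be calculated to quantify the impact of performing a cognitive task on physical performance".

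Testing takes place twice, before and after the intervention.

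**The concern.** Item (2) defines what 0 and 1 mean in the list that drives testing, so it is an instruction to the testers. It says which condition the motor task is done under. It does not say which condition comes first. A tester who follows it would give each woman one condition per visit.

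Dual-task performance is part of objective (a) and of H1, and it sits among the confirmatory outcomes. Dual-task cost is a within-woman contrast and does not exist unless she has performed both ways. A confirmatory outcome would then depend on testers reading past the written rule.

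**Working it through.** The plan states no figure on this point, so there is none to reproduce. The check compares the statements and then follows each reading.

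**Step 1. The statements side by side.**

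| Place | What is fixed |
|---|---|
| Section 2.3, opening | Order of conditions is randomised |
| Section 2.3, item (2) | Condition is randomised: single = 0, dual = 1 |
| Section 2.7 | Both conditions are administered |
| Section 2.13 | Both conditions are analysed; dual-task cost is calculated |

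The first, third and fourth rows agree with each other. Item (2) is the odd one out. Item (1) is worded as a position, so the authors could express order when they meant it.

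**Step 2. Literal reading.** Inputs: 22 women per arm (Section 2.2.2) and a fair 0/1 draw (Section 2.3).
- Women per arm doing the dual task at a visit: 22 × 0.5 = 11 expected, with the other 11 doing the single task.
- Women with both conditions at the same visit: 0, so no dual-task cost can be computed.
- If the draw were repeated at post-test, the share with dual-task data at both visits would be 0.5 × 0.5 = 25%, or about 5.5 of 22 per arm.
- If one draw were kept, arms could still be compared on dual-task change with about 11 women each. Within-woman cost would still be lost.

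**Step 3. Order reading.** Suppose whichever condition comes second gains an additive δ. The documents give no value for δ.
- *Dual-task performance.* Let a and b be 0 or 1 for dual done second at pre and post. The change gains (b − a)δ. If the order is kept, b = a and the term is zero. If it is redrawn, the mean is 0 and the variance is 2 × ¼ × δ² = δ²/2.
- *Dual-task cost, taken as dual minus single.* The order effect enters as ±δ at each visit. With a redraw the change gains 0 or ±2δ, with mean 0 and variance 2δ², four times as large.
- The order is drawn for each woman separately from the allocation of associations to arms, so the expected difference between arms is zero either way.

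**Step 4. Simulation and range.** Assumptions: 22 per arm, pre–post correlation 0.7, δ = 0.2 or 0.5 SD of the outcome, 20,000 runs, women treated as independent. The type I figures therefore speak only to the order effect, not to the clustering by association.

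| Order at post-test | δ | Mean difference between arms (SD) | Type I error |
|---|---|---|---|
| Kept | 0.2 | 0.000 | 0.049 |
| Kept | 0.5 | −0.001 | 0.051 |
| Redrawn | 0.2 | 0.000 | 0.050 |
| Redrawn | 0.5 | 0.003 | 0.050 |

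For dual-task performance with a redraw, the variance of the change is 2(1 − 0.7) + δ²/2, against 0.6 if the order is kept:
- δ = 0.2: 0.62 / 0.6 = 1.03
- δ = 0.5: 0.725 / 0.6 = 1.21

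Over correlations of 0.5 to 0.9 and both δ values the factor runs from 1.02 to 1.63.

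**The case against.** The strongest reply is that item (2) is loosely worded and nothing more. Section 2.3 itself says that the sequence is randomised, and Sections 2.7 and 2.13 take both conditions for granted. That reply stands as to intent. A reader might infer that half the women are meant to skip the dual task, and the documents do not support that. It does not rescue the rule, because only the coding sentence says what 0 and 1 stand for, and it says something else.

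A reader might also infer that, under the order reading, practice and fatigue become mixed with the training effect. The documents do not support this either. Randomising the order is the usual protection against such effects, and Step 3 shows no expected bias between arms. Section 2.3 also describes rest between alternating tests, "thereby ensuring adequate rest periods to prevent cumulative fatigue".

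Two further replies stand. Whether the list is reused at post-test is an operational detail that an article may leave to the full protocol, and a draw made per participant is compatible with reuse. Simple randomisation of test order is also legitimate. With 22 per arm there is a 17% chance that the arms differ by five or more women on starting condition. That is no separate harm: it cancels from the change if the order is kept, and it is already in the variance term if the order is redrawn. Blocking within association would be a preference.

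**Conclusion.** The contradiction is real and rests on the text alone: item (2) of Section 2.3 cannot stand beside its own opening sentence, Section 2.7 and Section 2.13. If it were applied as written, about 11 of 22 women per arm would do the dual task at a visit and dual-task cost could not be calculated for anyone. It would go too far to say that the dual-task part of H1 could not be tested at all, because a reduced comparison between arms would remain if the draw were kept.

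The order question is secondary. If the order were redrawn, the cost would be extra noise in the change, larger for dual-task cost than for dual-task performance. Its size rests on assumed order effects and correlations and on an assumed redraw, none of which the documents state.

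**What to change.** Replace item (2) with a statement that every woman performs the TUG, ACT and CST under both conditions at each visit, and that the code sets only which comes first: 0 = single-task first, 1 = dual-task first. This is a one-clause correction, with the code's meaning updated in the allocation file. It needs no extra tests and no extra participants.

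As a free refinement, say that codes (1) and (2) are drawn once per woman and reused at post-test, so that an additive order effect drops out of her pre–post change. The only downside is that the assessor has to look up the stored order at the second visit.
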